### Aims

This study represents the third, and last, phase (pilot 3) of large-scale pilots aiming to gradually co-design and iteratively test the PC4L integrated platform and modules.

While pilot phases 1 and 2 focused on technical feasibility and patients’ satisfaction, this protocol focuses on the following objectives:

To assess the impact of using the PC4L platform on patients’ quality of lifeTo compare the metrics generated by the PC4L platform in real-life conditions with the clinical outcome measuresTo evaluate the feasibility and safety of measuring disease progression and patient health status through the global functioning of the PC4L systemTo assess and compare the feasibility and usability of 2 different versions of the PC4L system (fully equipped version vs cloud-based solution)To increase patients’ safety and empowerment

As the primary outcome, the study will provide:

The difference in quality of life between groups (experimental vs control group), measured by the EQ-5D-3L scale at the end of the study

The following secondary outcomes will also be acquired:

The correlation coefficient of the PC4L platform metrics (eg, steps and physical activity levels, sleep, number of falls, cognitive scores) with the clinical outcome measures (eg, motor clinical evaluation, sleep questionnaire, Falls Efficacy Scale-International [FES-I], cognitive evaluations) measured at baseline, end of the study, and the values of change from baselineSystem usability assessment, measured through the System Usability Scale (SUS), at the end of the studyUsers’ satisfaction with the PC4L system, measured through a 5-point Likert Scale, the mHealth User Satisfaction Questionnaire, and the participants’ answers to open questions, at the end of the studyChanges in patients’ satisfaction and empowerment, measured by the Patient Assessment of Chronic Illness Care (PACIC) and the Short Assessment of Patient Satisfaction (SAPS) scales, respectively, at baseline and at the end of the studyChange in patients’ use of medical resources (number of admissions and number of days spent in health institutions) in the last month, measured at baseline and at the end of the study

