#### PC4L System Versions

Two different versions of the PC4L system were used (Figure 1): a fully equipped version, with all the devices enumerated above provided to the patients, and a cloud-based system that only requires a smartphone and a wearable sensor. Of those patients using the PC4L system, 25.1% (70/279) used the fully equipped version, whereas the remaining ones (209/279, 74.9%) used the cloud-based system.

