### Study Design

A prospective multicenter clinical study is conducted in 5 European countries: Germany, Italy, Portugal, Romania, and Spain (also including 6 pilot centers).

The pilot sites are (1) Asociacion Parkinson Madrid (APM), Madrid (Spain); (2) Casa di Cura del Policlinico (CCP), Milano (Italy); (3) Campus Neurológico Sénior (CNS), Lisbon (Portugal); (4) University and Emergency Hospital of Bucharest (UHB), Bucharest (Romania); (5) University of Medicine and Pharmacy (UMF), Bucharest (Romania); and (6) Wohlfahrtswerk für Baden-Württemberg (WBW), Stuttgart (Germany).

There are also 3 different scenarios: (1) rehabilitation center (inpatients and outpatients); (2) day care centers; and (3) home set (ie, patients’ home).

The duration per patient, at home and in the day care center, will be up to 3 months. Participants in the rehabilitation center participated during the period of their stay in the center (not exceeding the 3 months).

A specific route diagram is presented in Figure 2 in accordance with the CONSORT (Consolidated Standards of Reporting Trials) guidelines. The protocol of this study was developed in accordance with the SPIRIT (Standard Protocol Items: Recommendations for Interventional Trials) guidelines (Figure 3) [12]. The schedule of enrollment, interventions, and assessments is presented in Figure 3.

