### Recruitment

Patients with PD and other parkinsonian syndromes, AD, or ODs were invited to participate from the clinical centers involved in the study. Each participant organization was assigned to recruit a number of participants related to their skills, experience, number of researchers involved, and access to users (Table 2).

**Table 2 table2:** Distribution of participants per clinical center and scenario.

Scenario/clinical center	Rehabilitation (n=204), n	Day care (n=82), n	Home (n=272), n	Total (N=558), n
APM^a^	80	N/A^b^	26	106
CCP^c^	63	N/A	62	125
CNS^d^	46	N/A	86	132
UHB^e^	15	N/A	15	30
UMF^f^	N/A	30	30	60
WBW^g^	N/A	52	53	105

^a^APM: Asociacion Parkinson Madrid.

^b^N/A: not applicable.

^c^CCP: Casa di Cura del Policlinico.

^d^CNS: Campus Neurológico Sénior.

^e^UHB: University and Emergency Hospital of Bucharest.

^f^UMF: University of Medicine and Pharmacy.

^g^WBW: Wohlfahrtswerk für Baden-Württemberg.

To reach the planned number of recruits, many strategies were implemented: participants were contacted through online webinars; through brochures placed in specific centers such as pharmacies, leisure centers, and medical offices; and through patients’ associations. Further, regular updates were posted via online newsletters on different websites, such as the PC4L website and end users organizations’ websites. In addition, information about the PC4L pilot 3 study was shared during national and international conferences. Recruitment was also promoted in a collaborative way thanks to partners from other European projects. Finally, participants were recruited in person when accessing the medical facilities and via phone contact or emails after searching local databases.

Patients who discontinue the study participation because of medical conditions (ie, infections, falls, medical emergencies) or unwilling to participate any longer for other reasons (ie, difficulty with technology, loss of interest) will be considered dropouts.

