#### Intervention Group

The patients recruited and assigned to the experimental group received specific instruction in using the project platform, but without any specific program concerning the activities.

Specifically, patients, after the baseline assessment, received the instrumental setup and indications on its functionalities. Patients were instructed about the use of the Fitbit, the PC4L app, and the cognitive games on a tablet or computer. Patients were also provided with manuals.

Specifically, according to the study approach detailed by Biehl et al [9], the patients were instructed to complete the following questionnaires in the app during the first week and during the last week of the study period: the 10-item Eating Assessment Tool (EAT10) [13] for evaluation of dysphagia; the Edmonton Symptom Assessment System (ESAS) [14] and the Patient Global Impression (PGI)—Severity [15] for evaluation of symptoms; and the International Physical Activity Questionnaire (IPAQ) [16] for evaluation of physical activity. In addition, during the last week of using the app, patients were requested to complete the SUS [17], via the app, for evaluation of usability.

The platform was installed in each scenario with the assistance of the project research staff (ie, bioengineers).

A total of 2 versions of PC4L systems were installed: while the cloud-based system (which only required a smartphone and a wearable sensor) was used in all scenarios, a fully equipped version was implemented only in the rehabilitation scenario.

The patients received the same directions in all 3 scenarios.

At the end of the study period, patients performed end-of-study evaluations and returned the instrumental setup.

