### Statistical Analysis

Descriptive analysis will be performed for all variables to characterize the sample. For continuous variables, mean, SD, median, and range values will be calculated. For categorical variables, absolute and relative frequencies will be used to describe the data [29-31].

Normality will be studied using the Kolmogorov-Smirnov and Shapiro-Wilk tests. The effect of using the PC4L system will be analyzed by applying the paired-sample *t* test (2-tailed) and the Wilcoxon signed rank test to each variable (statistical significance will be set at P<.05).

The Pearson and Spearman correlation tests will be used to validate the PC4L systems metrics (statistical significance will be set at P<.05).

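### Platform metrics are validated by unadjusted correlation tests in users from three care settings; if run over all users together, these cannot separate within-setting tracking from differences between settings

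*Protocol article*

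**What the plan says.** The article gives one sentence to the validation method: "The Pearson and Spearman correlation tests will be used to validate the PC4L systems metrics", with the rule that "statistical significance will be set at P<.05" (Statistical Analysis). It names no covariate, stratum or partial correlation. The analysis serves the second objective in Aims and the first secondary outcome there, which begins "The correlation coefficient of the PC4L platform metrics" and covers baseline, end of study and change from baseline.

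The users are not one homogeneous group. Study Design says: "There are also 3 different scenarios: (1) rehabilitation center (inpatients and outpatients); (2) day care centers; and (3) home set". The documents tie three things to setting:

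- **Environment.** The Discussion describes rehabilitation centres as places of personalised motor and cognitive training under a multidisciplinary team. Day care is also supervised; home is not described that way.
- **Device version.** Under Intervention Group, "a fully equipped version was implemented only in the rehabilitation scenario". PC4L System Versions adds: "Of those patients using the PC4L system, 25.1% (70/279) used the fully equipped version". In Table 1 (Metrics), falls, festination and freezing draw on cameras as well as other sensors.
- **Observation time.** Study Design follows rehabilitation patients for their stay, capped at 3 months, and the others for up to 3 months.

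**The concern.** Validation should show that a metric such as steps or sleep follows the clinical state of the patient wearing the device. A Pearson or Spearman test has no place for a covariate. Its null is zero marginal correlation in whatever group it is run on. If that group spans three settings, the coefficient combines two things: how metric and scale move together among patients in the same setting, and how the setting averages line up.

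If setting shifts both variables the same way, a metric unrelated to the scale within every setting can pass. If it shifts them in opposite ways, a metric that does track the scale can fail. The significance rule cannot tell these cases from genuine success or failure. At stake is a secondary outcome, namely which metrics the trial reports as agreeing with clinical measures.

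**Working it through.** The plan states no figure for the correlation analysis, so there is none to reproduce. The 558 patients and 95% power in Sample Size refer to EQ-5D-3L.

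**Inputs from the documents.** There are 279 system users. Table 2, whose rehabilitation column is headed "Rehabilitation (n=204), n", gives 204 in rehabilitation, 82 in day care and 272 at home over both arms.

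**Assumptions.**
- Arms are balanced within setting: 204/2 = 102, 82/2 = 41, 272/2 = 136, total 279.
- Tests are two-sided at 0.05 (the sidedness of the correlation tests is not stated), with no dropout.
- Setting moves each variable by d within-setting SDs; d is varied because the documents give no value.

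**Step 1: significance threshold.** With n = 279, t = 1.969 on 277 df, so critical |r| = t/√(n − 2 + t²) = 1.969/√(277 + 3.88) = 0.117. A weak coefficient is enough.

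**Step 2: what a shift does to the pooled coefficient.** Let rehabilitation differ from the other two settings by d in both variables. With w = 102/279 = 0.366, the between-setting variance is c = w(1 − w)d² = 0.232d². For within-setting correlation ρ:

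- same direction: r = (ρ + c)/(1 + c)
- opposite direction: r = (ρ − c)/(1 + c)

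For ρ = 0 and same direction, d = 0.3 gives 0.0209/1.0209 = 0.020; d = 0.5 gives 0.058/1.058 = 0.055; d = 0.8 gives 0.148/1.148 = 0.129, which is already above 0.117. For ρ = 0.2 and opposite direction, d = 0.5 gives 0.142/1.058 = 0.134, and d = 0.8 gives 0.052/1.148 = 0.045.

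**Step 3: rejection rates by simulation.** Two shift patterns were used: rehabilitation against the other two settings (A), and rehabilitation and home d apart with day care midway (B).

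| Case | d | Pooled Pearson, A | Pooled Pearson, B | Within-setting test |
|---|---|---|---|---|
| ρ = 0, same direction | 0.3 | 6.3% | 6.3% | about 5% |
| | 0.5 | 15.7% | 12.7% | about 5% |
| | 0.8 | 59.0% | 51.6% | about 5% |
| ρ = 0.2, opposite | 0 | 92.3% | – | 92% |
| | 0.3 | 84.5% | – | 92% |
| | 0.5 | 61.5% | 66% | 92% |
| | 0.8 | 12.0% | 15% | 91-92% |

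Under ρ = 0, pooled Spearman is within two percentage points of Pearson (57.3% at d = 0.8 in A), so ranks give no protection. If only one variable shifts, by 0.5 or 1.0 SD, pooled Pearson rejects in 5.1-5.2%.

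**Step 4: cross-check of A with Fisher's z.** The test statistic has mean atanh(r)·√276 = 16.61·atanh(r). For d = 0.8 and ρ = 0: 16.61 × 0.130 = 2.16, and Φ(2.16 − 1.96) ≈ 58%, against 59.0% simulated. For ρ = 0.2 and no shift: 16.61 × 0.203 = 3.37, and Φ(1.41) ≈ 92%. For ρ = 0.2 and opposite shifts of 0.5: 16.61 × 0.135 = 2.24, and Φ(0.28) ≈ 61%, against 61.5%.

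**The case against.** The strongest reply is that pooling is inferred. The sentence names tests, not an analysis population, and a full protocol or SAP could specify correlations by setting. That stands as a limit: a reader might infer that the plan commits to pooling, but no section says so. The article does fix the tests and the decision rule, and neither test can adjust for setting.

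Second, a reader might take it as documented that the settings recruit patients with different clinical scores, or that a rehabilitation stay dictates activity and sleep. Neither is shown. No scores are reported by setting, diagnostic and staging criteria are common to all scenarios, and rehabilitation includes outpatients. The shifts remain assumptions. False validation needs both variables to shift, and lost power of the size shown needs opposite shifts.

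Third, marginal association is not plainly the wrong target. Aims speaks of comparing metrics with clinical measures in real life. If settings differ in true severity and the metric follows it, that is evidence of validity. This stands, and is why the pooled coefficient should be kept rather than demoted.

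Fourth, constant level shifts cancel in the change-from-baseline correlations. That is correct. Setting-dependent change would still confound them, and a rehabilitation programme may plausibly produce it, but the simulations do not model it. A reader may also note that a pooled r near 0.13 looks weak whatever its P value; the stated rule nevertheless counts it as significant.

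Finally, not every metric is affected. Loss of balance is measured by cameras only (Table 1), and Instrumental Setup places the cameras in the rehabilitation centres, so it cannot be pooled over three settings.

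**Conclusion.** The point holds conditionally. The plan validates metrics with unadjusted tests while environment, device version and observation time vary with setting. If all users are analysed together, a significant coefficient does not show within-setting tracking, and a non-significant one does not rule it out.

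The size depends on shifts that the documents do not give. It is material from about 0.5 SD in both variables: false rejection of 13-16% at 0.5 SD and 52-59% at 0.8 SD, or power down from about 92% to 62-66% and 12-15% when the shifts oppose and the within-setting correlation is 0.2. At 0.3 SD false rejection is about 6%. The figures also assume balanced arms within setting and all 279 users contributing data.

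It would go too far to say that setting differences are part of the test's null, or that metrics will be wrongly validated. The null is zero marginal correlation, and the documents do not show that the conditions for harm are met. This is an inexpensive improvement to a secondary outcome; the primary EQ-5D-3L comparison is unaffected.

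**What to change.** State whether the correlations are pooled or within setting, and add to Statistical Analysis, for metrics measured in more than one setting:

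*Beside each pooled coefficient, the partial Spearman coefficient adjusted for scenario (rehabilitation, day care, home) and the scenario-specific coefficients will be reported with 95% confidence intervals. A metric will be called validated across settings only if the association also holds within settings.*

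Do the same by diagnosis only where the clinical scale is applied across diagnoses. The article describes MDS-UPDRS for PD and CDRS for AD and other dementias, so diagnosis adjustment has little or no role there.

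The cost is small. Scenario is already known for every patient, so no new data are needed. Adjustment uses about two degrees of freedom, and the simulated within-setting power stayed at 91-92% for a correlation of 0.2. Intervals will be wider in the smaller settings: with about 41 day-care users, |r| must exceed 0.308 for significance, against 0.195 with 102 and 0.168 with 136, so the scenario-specific values should be read through their intervals. Coefficients will also be somewhat lower where setting itself reflects severity, which is why the pooled values stay in the report.

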**Results:**

The study protocol is part of a project approved and funded by the European Commission Horizon 2020 (grant agreement number 875221). The ethics committees of all involved centers reviewed and approved the study protocol. The study began with the recruitment phase in September 2022, and enrollment ended in February 2023. Recruitment is now closed (April 2023). The results of this study are expected to be published in summer 2023. A total of 558 patients, 279 per study group, were recruited. The results will allow to clarify the impact of PC4L on quality of life, will assess the empowerment of patients and the medical resources use, as well as the usability of the final version of the PC4L system. It will also provide information on the support of the system as a tool to facilitate the decision-making process.

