#### Metrics

During the monitoring period, specific metrics (Table 1) are collected, continuously and passively, through the PC4L system.

**Table 1 table1:** Metrics and related devices used during patients’ monitoring.

Metrics	Devices
Walking parameters	Wristband and phone
Bradykinesia	Wristband and phone
Loss of balance	Cameras
Falls	Cameras and wristband
Festination	Wristband and phone and camera
Physical activity	Wristband
Freezing	Wristband and phone and camera
Inactivity	Wristband
Compliance with medication	App
Sleeping pattern	Wristband
Interaction patterns with the devices	Platform or app
Usage of the physical activity recommendation services	Number of clicks per week of the different services

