### Randomization

Patients were randomized in a ratio of 1:1 to the intervention group (use the PC4L system) or the control group (no intervention) by an independent, nonclinical partner of the project consortium.

Patients allocated in the intervention group were randomized in a ratio of 3:1 to the “cloud-based solution” and the “fully equipped” PC4L system version.

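### P<.05 on a correlation is the only stated criterion for validating the platform metrics, and a coefficient of about 0.12 meets it if all 279 intervention patients contribute

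*Protocol article*

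**What the plan says.** The Statistical Analysis section of the protocol article assigns the correlations a purpose and a significance level: "The Pearson and Spearman correlation tests will be used to validate the PC4L systems metrics (statistical significance will be set at P<.05".

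The analysis serves the first secondary outcome listed under Aims: "The correlation coefficient of the PC4L platform metrics (eg, steps and physical activity levels, sleep, number of falls, cognitive scores) with the clinical outcome measures", at baseline, at the end of the study and for the change between them. No value of the coefficient is named as sufficient. The article also gives no confidence-limit requirement and no agreement analysis for these metrics. Usability is treated differently: the Usability and Satisfaction Assessment section sets a benchmark, an SUS score above 68.

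On who supplies platform data:
- The abstract's Results: "A total of 558 patients, 279 per study group, were recruited".
- Randomization: "Patients were randomized in a ratio of 1:1 to the intervention group (use the PC4L system) or the control group (no intervention".
- PC4L System Versions: "25.1% (70/279) used the fully equipped version, whereas the remaining ones (209/279, 74.9%) used the cloud-based system".
- Table 1, under Metrics, lists one metric as coming from the cameras alone: "Loss of balance Cameras".

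**The concern.** A correlation test at the 5% level asks whether the coefficient differs from zero. Validation asks something else: whether the metric follows the clinical measure closely enough to be useful. With a few hundred patients, very weak relations pass the first test while saying little about the second.

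The smallest coefficient that passes also depends on how many patients supply both measurements, and that number differs between metrics. One observed correlation could count as validation for a wristband metric and as failure for a camera metric.

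Comparing platform metrics with clinical measures is one of the stated objectives, and the Discussion presents validation in real-life use as the project's final scope. A claim of validated metrics that rested on this criterion could be little more than a statement about sample size.

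**Working it through.** The plan has no figure of its own to reproduce here: no target coefficient, n or power is given for the correlations. The 558 in the Sample Size section belongs to the EQ-5D-3L outcome.

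**Inputs**
- Alpha 0.05 (Statistical Analysis). Sidedness is not stated for the correlations; two-sided is assumed, as for the t test in the same section.
- n at most 279, since controls do not use the platform (Randomization).
- n = 209 for the cloud-based users (PC4L System Versions).
- n at most about 70 for camera-only metrics. The cloud-based version needs only a smartphone and a wearable, and the 70 fully equipped users are the remainder.
- n = 140, about half of 279, as an assumed disease subgroup. The number per disease is not stated.

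**Smallest significant Pearson coefficient**

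r = t / √(n − 2 + t²), with t the two-sided 5% point on n − 2 degrees of freedom.

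- n = 279: 1.969 / √(277 + 3.877) = 0.1175; r² = 0.014
- n = 209: 1.972 / √(207 + 3.889) = 0.136; r² = 0.018
- n = 140: 1.977 / √(138 + 3.909) = 0.166; r² = 0.028
- n = 70: 1.995 / √(68 + 3.980) = 0.235; r² = 0.055

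For Spearman, the Fisher z approximation with the standard error inflated by 1.03 gives about 0.121 at n = 279 and 0.242 at n = 70. At n = 279, a Pearson coefficient exactly at the threshold has a 95% confidence interval of about 0.00 to 0.23. An observed 0.18 passes at n = 279 and fails at n = 70.

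**Chance that a weak relation passes**

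Fisher z: probability ≈ Φ[(atanh ρ − atanh r) × √(n − 3)], with r the threshold above.

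- True ρ = 0.20 (4% shared variance), n = 279: (0.2027 − 0.1180) × √276 = 1.41, so 92%.
- True ρ = 0.15, n = 279: 71%.
- True ρ = 0.20, n = 70: (0.2027 − 0.2397) × √67 = −0.30, so 38%.

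**What a strength criterion would require**

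For a lower 95% limit above a minimum m, the observed r must exceed tanh(atanh m + 1.96/√(n − 3)). With m = 0.3, an assumed value for illustration only:

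- n = 279: tanh(0.3095 + 0.1180) = 0.40
- n = 70: tanh(0.3095 + 0.2395) = 0.50

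**The case against.** The strongest reply is that the article never says a metric is declared valid once P<.05. The significance level stands in parentheses, the same parenthesis follows the tests of the intervention effect, and Aims makes the coefficient itself the outcome. Readers will see its size. This stands in part: weak metrics could be called validated, but nothing says they will be. It does not remove the problem, because validation is the stated purpose and no other criterion appears.

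A second reply is that a journal article leaves much to an analysis plan. That holds for the full list of pairs and for multiplicity rules, and their absence is not held against the article. The link between validation and P<.05, however, is stated in the article rather than left out.

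Third, 0.12 is the full-n case. MDS-UPDRS is for PD and CDRS for AD and other dementias, and the sample size made no allowance for dropout, so many comparisons will have fewer patients and a higher threshold. This is correct. Even so, between n = 209 and n = 70 the threshold is only about 2% to 6% of variance.

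Fourth, a lower-limit rule also depends on n (0.40 against 0.50 above). That is true. The difference is that, as n grows, the required coefficient falls towards the chosen minimum instead of towards zero.

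Two stronger readings should be resisted. A reader might cross every Table 1 metric with every scale and predict many chance validations. Aims lists metrics and comparators in matching order, which suggests four pairs; the lists are only examples, but four pairs at three time points make 12 tests, or 12 × 0.05 = 0.6 expected passes if no relation exists. Some Table 1 rows, such as clicks per week, have no listed comparator. A reader might also infer that the decision support rests on these correlations. The Decision Support System section describes sensor, game and questionnaire inputs, fusion modelling and clinical supervision, and makes none of it conditional on them.

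**Conclusion.** The concern holds as a badly fixed criterion for a stated objective. "statistical significance will be set at P<.05" is the only criterion attached to validation, and it is met by about 0.12 (1.4% shared variance) if all 279 intervention patients contribute and by about 0.24 (5.5%) at n = 70. With full n, a true correlation of 0.20 would pass 92% of the time. These figures assume two-sided tests and complete data at the stated n; the actual n per metric and per disease group is not given.

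The primary EQ-5D-3L comparison and its sample size are not affected. The documents do not support saying that weak metrics will inevitably be declared valid.

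**What to change.** Drop P<.05 as the validation criterion. For the pairs indicated under Aims (activity with motor evaluation, sleep with the sleep questionnaire, falls with FES-I, cognitive scores with cognitive evaluations):
- report the coefficient with its 95% confidence interval and the n behind it;
- where the scale is disease-specific, do this within the relevant disease group;
- call the metric valid only if the lower confidence limit exceeds a minimum strength that the consortium fixes for that pair before the correlations are computed.

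The minimum need not be the same for every pair: FES-I, for example, measures fear of falling, not falls. Treat all other pairs as exploratory.

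The cost is a change of analysis wording, with no new data. Fewer metrics will be declared valid, and metrics with small n will need a higher observed coefficient.
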